## 6.5. Follow-Up

### 6.5.1. Safety Follow-Up

The safety follow-up period is the interval between the EOT visit and the scheduled follow-up visit, which should occur 180 days after the EOT visit (or after the last dose of study drug if the EOT visit was not performed). Adverse events and SAEs must be reported up until at least 30 days after the last dose of study drug, the date of the follow-up visit, or until toxicities resolve, return to baseline, or are deemed irreversible, whichever is longer.

If a subject withdrew from treatment due to reasons other than disease progression, GVHD staging and grading will be repeated at the safety follow-up visit.

### 6.5.2. Post-Treatment GVHD Follow-Up

Subjects who completed study treatment or discontinued treatment for reasons other than GVHD progression will be followed every 28 days (± 7 days) after the safety follow-up visit until any of the following occurs:

- GVHD progression.
- Initiation of a new anti-GVHD therapy.
- Relapse/recurrence of underlying hematologic disease.
- A maximum of 12 months from EOT or a maximum of 24 months from Day 1 is

reached, whichever occurs first.

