| \| **Primary Objective** \| **Primary Endpoint** \| \| --- \| --- \| \| Compare the efficacy of ruxolitinib in combination with corticosteroids versus corticosteroids in terms of overall response rate (ORR) at Day 28 in subjects with acute graft-versus-host disease (acute GVHD). \| ORR at Day28, defined as the proportion of participants demonstrating a complete response (CR), or partial response (PR) \| \| **Secondary Objective** \| **Secondary Endpoints** \| \| Compare additional response and longer-term efficacy outcomes between treatment cohorts. \| Durable ORR at Day56, defined as the proportion of patients in each arm whose response on day 28 lasts until day 56 after randomization. \| \| DOR at Month 6 for responders will be calculated. The DOR is defined from the time of the onset of response to loss of response. Subjects who died or discontinued will be censored at the  death date or the previous assessment. \| \| Response duration, defined as the time from the first response to the first recurrence/progression of acute GVHD or additional immunosuppressants for GVHD. \| \| NRM at Month 24, defined as the time from enrollment to death due to any causes other than hematologic disease relapse. \| \| Cumulative incidence of relapse (CIR) at Month 24, defined as the proportion of subjects whose underlying hematologic disease relapses. \| \| Disease-free survival (DFS) at Month 24, defined as the time from enrollment to relapse of primary disease or death from any causes, whichever occurred first. \| \| Failure-free survival (FFS) at Month 24, defined as the time from randomization to disease relapse or progression, non-relapse mortality, or the addition of new therapy for acute GVHD. \| \| Overall survival (OS) at Month 24, defined as the time from randomization to death due to any causes. \| \| Assess the incidence and severity of adverse events (AEs) and serious adverse events. \| Clinical safety data (eg, AEs, infections) will be tabulated and listed. \| \| Evaluate the use and discontinuation of  corticosteroids. \| Average and cumulative corticosteroid dose at Days 365; \| \| Evaluate the use and discontinuation of  immunosuppressive medications. \| Proportion of subjects who discontinue immunosuppressive medications at Days365. \| \| Evaluate the incidence of recurrent acute GVHD \| Incidence rate of recurrent acute GVHD through Month 24. \| \| Evaluate the incidence of cGVHD. \| Incidence rate of cGVHD at Month 24. \| \| **Overall Study Design:**  This trial is an open-label, multicenter, prospective randomized two-arm phase II study comparing the efficacy and safety of ruxolitinib plus methylprednisolone (1 mg/kg) vs. methylprednisolone (2 mg/kg) alone. The biomarkers of acute GVHD, such as sST2, sTNFR1, IL-6, IL-8, and REG3α will be tested at acute GVHD onset. Patients with newly diagnosed intermediate-risk or high-risk acute GVHD, as defined by Minnesota acute GVHD risk score and the biomarker score will be included. The treatment efficacy will be evaluated with respect to the level of biomarkers and clinical manifestations. Written informed consent must be obtained from the patients before enrollment in the study. The consent form and related materials are available from the corresponding author on request.  **Study Population:**  Eligible patients with intermediate-risk or high-risk acute GVHD graded according to the modified Glucksberg criteria, Minnesota acute GVHD risk score and the biomarker score and untreated with systemic acute GVHD therapy will be enrolled in this study.  **Key Inclusion Criteria:**   - Male or female, 14 to 65 years old. - Have undergone first allogeneic hematopoietic stem cell transplantation (allo-HSCT) from any donor source using bone marrow, peripheral blood stem cells, or cord blood for hematologic malignancies. - Develop a de novo acute GVHD, defined as intermediate- or high-risk using the Minnesota acute GVHD risk score and MAGIC biomarker algorithm.   **Key Exclusion Criteria:**   - Has received more than one allogeneic stem cell transplant. - Female patients with pregnant or breast-feeding. - Has Acquired Immune Deficiency Syndrome (AIDS), or hepatitis B/C infection, uncontrolled bacterial, fungal, or viral infections. - Allergies to ruxolitinib. - Vital organ dysfunction unrelated to GVHD, including persistent bilirubin abnormalities or severe heart and respiratory diseases. - Relapse of the primary disease or graft rejection after transplantation. - Presence of GVHD overlap syndrome. - Presence of cGVHD or associated clinical signs or DLI-induced acute GVHD or interferon. - Previous history of JAK1/2 inhibitor treatment after transplantation, except JAK inhibitors administered before the transplantation. - absolute neutrophil count (ANC) <0.5×10^9^/L or platelet count (PLT) < 20×10^9^/L - Serum creatinine > 2.0 mg/dL or creatinine clearance < 40 mL/min measured or calculated by Cockroft-Gault equation. - Patients with poor compliance should not be included in the study based on the judgment of the research team, for example if they refused to take medicine at will many times during the previous treatment.   **Study Drug, Dosage, and Mode of Administration:**  **Ruxolitinib plus corticosteroids treatment (ruxolitinib group):**  The initial dose of methylprednisolone is 1 mg/kg/day intravenously given in this arm for at least 7 days. The dosage of ruxolitinib is 5 mg PO QD. CSA will be administered intravenously at a dose of 2 mg/kg twice daily, targeting minimum concentration levels of 150–250 ng/mL. If GVHD response to treatment is assessed as PR/CR at 7 days, methylprednisolone will be tapered, followed by reduction and discontinuation of CSA and then ruxolitinib. The reduction of the methylprednisolone in the ruxolitinib group is gradual, suggesting it be tapered off over 6 weeks as follows: dosage reduced to 0.6 mg/kg/day, 0.4 mg/kg/day, 0.3 mg/kg/day, 0.25 mg/kg/day, and 0.18 mg/kg every 5 days, followed by 0.1 mg/kg/day at week 4, 0.1 mg/kg every other day after 5 days and stopped at week 6. After steroid discontinuation and CR or stable PR maintained for 6 weeks, CSA is tapered over 60 days. After CSA discontinuation and no presence of recurrent GVHD, ruxolitinib is tapered off over 90 days, which is totally maintained for approximately 6 months.  **Corticosteroid treatment (corticosteroids group):**  The initial dose of methylprednisolone is 2 mg/kg/day given twice daily for at least 7 days and then reduced. The dosage of methylprednisolone in the corticosteroids group is decreased gradually after CR and tapered off over 10 weeks as the following: dosage reduced to 1 mg/kg/day to 0.6 mg/kg/day, 0.4 mg/kg/day, 0.3 mg/kg/day, 0.25 mg/kg/day, and 0.18 mg/kg every 7 days, and then 0.1 mg/kg/day at week 4, 0.1 mg/kg every other day after 5 days, and stopped at week 10. CsA was administered intravenously at a dose of 2 mg/kg twice daily, targeting minimum concentration levels of 150–250 ng/mL. The recommended duration of CsA is 6 months.  In both arms, for refractory acute GVHD, i.e., the progression of GVHD after 3 days of therapy, no improvement within 7 days, or no CR after 14 days of therapy, the second-line therapy will be started. For refractory acute GVHD or recurrent acute GVHD, basiliximab may be used as second-line therapy, and other alternative drugs included methotrexate or mesenchymal stem cells may be used at the researcher’s decision. For refractory acute GVHD, methylprednisolone is discontinued and CsA is continued in both arms. Prolonged maintenance of ruxolitinib is used in the ruxolitinib group. A standardized follow-up booklet is given to each enrolled patient for recording the dose, frequency, and administration method of the drugs. **Estimated Duration of Participation:** Subject participation is expected to average 24 months, which includes the following:   - A screening period lasting up to 28 days. - A treatment period lasting as long as the subject is benefiting from treatment. - A safety follow-up period lasting 180 days after treatment ends. - A survival follow-up period lasting until death or study withdrawal. \| \| \| **Estimated Number of Subjects:** 198 subjects. \| \| \| **Principal Coordinating Investigator:** [name] \| \| \| **Statistical Methods:**  The sample size is calculated according to the primary endpoint (ORR) of the study. Based on our published phase I study of 32 acute GVHD patients who received steroids as first-line therapy, an expected proportion of 55% for the patients treated with corticosteroids only was established. Based on our published data of patients with acute GVHD grade I–IV who received steroid-ruxolitinib (5 mg/day) as first-line therapy, the ORR was 82.05%. Patients with acute GVHD grade I were also included in the phase I analysis. Thus, an expected proportion of 75% for the patients treated with steroid-ruxolitinib (5mg/day) was established. This study is planned to detect a response difference between treatment arms at a two-sided significance level α=5% with a power of 1-β=80%. The sample size was estimated using PASS software based on the primary endpoint (ORR). Allowing a withdrawal rate of 10%, 198 patients (99/group) will be required.  Continuous data are described as median with interquartile range (IQR) or mean and standard deviation (SD) according to the normality of distribution. The categorical data are described as n (%). The ORR was calculated with its 95% confidence interval (CI) and compared by the stratified Cochran–Mantel–Haenszel test. Additionally, a logistic regression model, which included aGVHD risk (high vs. intermediate), and disease status before transplantation (CR vs. no CR) as covariates, was established to explore the association between treatment and ORR on day 28. Post-hoc subgroup analysis was performed by biomarker risk, age and GVHD grade, although these were not prespecified in the protocol. The cumulative incidence of recurrent aGVHD was analysed using the Fine and Gray test in a competing risk framework. The Kaplan–Meier method was used to estimate the ORR on day 56, OS, DFS, and FFS, and the log-rank test was used to evaluate the difference between the groups. The cumulative incidence rates of NRM and relapse were estimated using a competing risk model and compared using the Fine and Gray test. A Cox proportional hazard regression model was used for multivariable regression analysis for OS and DFS. Multivariable regression analysis was performed for NRM using the Fine–Gray proportional hazard regression for competing events. The following variables were included in the univariable analysis: primary disease, cytogenetic risk, age and gender of the donor and recipient, source of graft, treatment arm, aGVHD risk, and disease status before transplantation. Variables with P<0.1 in univariate analysis or variables known to influence the outcomes were included in the multivariable analysis. Competing events were defined as follows: for GVHD, death without the event; for relapse, death without relapse; and for NRM, relapse. Any difference for which the two-sided P<0.05 was considered statistically significant. All analyses were carried out using SPSS 22.0 software (IBM Corporation, Armonk, NY, USA) or R version 4.1.2 (www.cran.r-project.org). All statistical analyses were based on the intend to treat set. \| \| | |

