# 2. STUDY OBJECTIVES AND ENDPOINTS

| Primary Objective | Primary Endpoint |
| --- | --- |
| Compare the efficacy of ruxolitinib in combination with 1mg/kg methylprednisolone versus 2 mg/kg methylprednisolone alone in terms of overall response rate (ORR) at Day 28 in subjects with acute graft-versus-host disease (acute GVHD). | ORR at Day28, defined as the proportion of participants demonstrating a complete response (CR), or partial response (PR) |
| Secondary Objective | Secondary Endpoints |
| Compare additional response and longer-term efficacy outcomes between treatment cohorts. | Durable ORR at Day56, defined as the proportion of patients in each arm whose response on day 28 lasts until day 56 after randomization. |
|  | DOR at Month 6 for responders will be calculated. The DOR is defined from the time of the onset of response to loss of response. Subjects who died or discontinued will be censored at the  death date or the previous assessment. |
|  | Response duration, defined as the time from the first response to the first recurrence/progression of acute GVHD or additional immunosuppressants for GVHD. |
|  | NRM at Month 24, defined as the time from enrollment to death due to any causes other than hematologic disease relapse. |
|  | Cumulative incidence of relapse (CIR) at Month 24, defined as the proportion of subjects whose underlying hematologic disease relapses. |
|  | Disease-free survival (DFS) at Month 24, defined as the time from enrollment to relapse of primary disease or death from any causes, whichever occurred first. |
|  | Failure-free survival (FFS) at Month 24, defined as the time from randomization to disease relapse or progression, non-relapse mortality, or the addition of new therapy for acute GVHD. |
|  | Overall survival (OS) at Month 24, defined as the time from randomization to death due to any causes. |
| Assess the incidence and severity of adverse events (AEs) and serious adverse events. | Clinical safety data (eg, AEs, infections) will be tabulated and listed. |
| Evaluate the use and discontinuation of  corticosteroids. | Average and cumulative corticosteroid dose at Days 365; proportion of subjects who discontinue corticosteroids at Days 56 and 100. |
| Evaluate the use and discontinuation of  immunosuppressive medications. | Proportion of subjects who discontinue immunosuppressive medications at Days 365. |
| Evaluate the incidence of recurrent acute GVHD. | Incidence rate of recurrent acute GVHD through Month 12. |

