| Evaluate the incidence of cGVHD. | Incidence rate of cGVHD at Month 24. |

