## 4.6. Duration of Treatment and Subject Participation

After signing the informed consent form (ICF), screening assessments may be completed over 1-2 days. Each subject enrolled in the study may continue to receive study treatment as long as benefit is being observed and/or treatment withdrawal criteria are not met. If the subject discontinues study treatment, the treatment period will end, and the subject will enter the follow-up period. The safety follow-up period will last 365 days, and the survival follow-up period will last until death or study withdrawal. Study participation is expected to average approximately 24 months per individual subject but may vary based on clinical outcomes.

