**7.4.1.2. Reporting**

Adverse events that begin or worsen after informed consent should be recorded on the Adverse Events form of the eCRF. Conditions that were already present at the time of informed consent should be recorded on the Medical History form in the eCRF. Monitoring for the occurrence of new AEs should be continued for at least 30 days after the last dose of study drug. Adverse events (including laboratory abnormalities that constitute AEs) should be described using a diagnosis whenever possible rather than by individual underlying signs and symptoms. When a clear diagnosis cannot be identified, each sign or symptom should be reported as a separate AE.

The term “disease progression” should be recorded as an AE/SAE itself only if there are no other identifiable AEs/SAEs associated with the disease progression at the time of reporting. For events associated with disease progression, the relevant signs and symptom should be reported using a diagnosis whenever possible, rather than the individual underlying signs and symptoms. When a clear diagnosis cannot be identified, each sign or symptom should be reported as a separated AE. If the events

resulting from disease progression meet the criteria for an SAE (eg, resulted in hospitalization, a life-threatening event, or death), the specific event(s) should be reported as an SAE(s). In both cases (ie, AEs or SAEs related to disease progression), for each event it should be indicated whether the event (diagnosis or signs and symptoms) is related to disease progression.

The severity of AEs will be assessed using CTCAE v4.0 Grades 1 through 5. If an event is not classified by CTCAE, the severity of the AE will be graded according to the scale below to estimate the grade of severity.

| **Grade 1** | Mild; asymptomatic or mild symptoms; clinical or diagnostic observations only; intervention not indicated. |
| --- | --- |
| **Grade 2** | Moderate; minimal, local, or noninvasive intervention indicated; limiting age-appropriate activities of daily living. |
| **Grade 3** | Severe or medically significant but not immediately life-threatening; hospitalization or prolongation of hospitalization indicated; disabling; limiting self-care activities of daily living. |
| **Grade 4** | Life-threatening consequences; urgent intervention indicated. |
| **Grade 5** | Death due to AE |

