### 7.5.2. Chronic GVHD Assessment

Subjects will be assessed for signs and symptoms of cGVHD according to local institutional practice at screening, during the treatment phase, at the end of treatment, and during re-treatment (if applicable). Definitive and possible manifestations of cGVHD should be assessed as per NIH consensus guidelines for cGVHD^[32]^.

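### Chronic GVHD is a Month-24 endpoint, but GVHD follow-up is counted from end of treatment and on the planned tapers stops before Month 24, possibly 3.5–5.5 months sooner in controls

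*Protocol*

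**What the plan says.** **Endpoints.** Protocol Section 2 lists "Incidence rate of cGVHD at Month 24", and the synopsis agrees. For recurrent acute GVHD the two differ: "Incidence rate of recurrent acute GVHD through Month 12" in Section 2 and "Incidence rate of recurrent acute GVHD through Month 24" in the synopsis.

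**GVHD observation.** Section 6.5.2 continues post-treatment GVHD follow-up until progression, new anti-GVHD therapy, relapse, or the point at which "A maximum of 12 months from EOT or a maximum of 24 months from Day 1 is" reached, whichever is first. Section 7.5.2 gives the cGVHD assessment times as "at screening, during the treatment phase, at the end of treatment, and during re-treatment (if applicable". Survival contacts in Section 6.5.3 may be by telephone or email and collect only new GVHD therapy and survival status. Section 7.5 describes post-treatment evaluation lasting 6 months. Section 7.5.1 grades acute GVHD from randomisation, including Day 365. For subjects who withdrew for reasons other than progression, it continues 28-day grading into survival follow-up with no 12-month limit.

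**Safety observation.** Section 6.5.1 places the safety visit, "which should occur 180 days after the EOT visit", and runs AE reporting to the longest of that visit, 30 days after the last dose, or resolution. The synopsis also gives 180 days. Section 4.6 says "The safety follow-up period will last 365 days".

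**End of treatment.** Section 6.2 ends treatment at permanent discontinuation of study drug. Section 7.4.2.2 names the study drugs as ruxolitinib and the corticosteroid, but cyclosporine (CsA) is described for both arms under the Section 5.1 heading on study drugs. EOT is not defined specifically for the control arm.

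**The concern.** A Month-24 incidence needs patients observed for cGVHD to Month 24. The rules in Sections 6.5.2 and 7.5.2 count from the end of study drug, and the planned treatment lengths differ by arm. Two things are at stake. The stated endpoint may not be obtainable from the data the protocol tells sites to collect. And the arm that stops treatment sooner may be observed for less time, so that fewer cGVHD events are recorded in it for that reason alone. AE reporting is anchored to EOT in the same way.

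**Working it through.** **Inputs.** Ruxolitinib arm (Section 5.1.1): at least 7 days of initial steroid, steroid taper of 6 weeks (42 days), response held for 6 weeks (42 days), CsA taper of 60 days, ruxolitinib taper of 90 days, stated total about 6 months. Control arm (Section 5.1.2): at least 7 days of initial steroid, taper of 10 weeks (70 days) after CR, CsA for 6 months. One month is taken as 30.44 days.

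**The plan's own figure.** The stated 6 months of ruxolitinib is roughly reproduced if the 6-week response period overlaps the steroid taper: 42 + 60 + 90 = 192 days, or 49 + 60 + 90 = 199 days (6.3–6.5 months). With the steps in series it is not: 42 + 42 + 60 + 90 = 234 days, or 241 days with the first 7 added (7.7–7.9 months). All readings are carried forward.

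**End of GVHD follow-up under Section 6.5.2** = the smaller of EOT + 12 months and 24 months.

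| Reading of EOT | EOT, days | EOT, months | Follow-up ends, month |
|---|---|---|---|
| Control: steroid stops at week 10 from Day 1 | 70 | 2.3 | 14.3 |
| Control: 7 + 70 | 77 | 2.5 | 14.5 |
| Control: CR at Day 28 (assumption), 28 + 70 | 98 | 3.2 | 15.2 |
| Control: CsA counted, 6 months | 183 | 6.0 | 18.0 |
| Ruxolitinib: stated 6 months | 183 | 6.0 | 18.0 |
| Ruxolitinib: overlapping steps | 192–199 | 6.3–6.5 | 18.3–18.5 |
| Ruxolitinib: steps in series | 234–241 | 7.7–7.9 | 19.7–19.9 |

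The shortfall to Month 24 runs from 24 − 19.9 = 4.1 to 24 − 14.3 = 9.7 months. Only a patient whose EOT falls at Month 12 or later would be followed to Month 24 under this rule.

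**Gap between arms.** Against control EOT at Day 70–77:
- stated 6 months: (183 − 77)/30.44 to (183 − 70)/30.44 = 3.5–3.7 months
- overlapping steps: (192 − 77)/30.44 to (199 − 70)/30.44 = 3.8–4.2 months
- steps in series: (234 − 77)/30.44 to (241 − 70)/30.44 = 5.2–5.6 months

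With control CR at Day 28 the gap is 2.8–4.7 months. With CsA counted as control study treatment it is 0–1.9 months.

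**cGVHD under Section 7.5.2 taken literally.** Assessment stops at EOT: about 2.3–2.5 months in controls and 6.0–7.9 months with ruxolitinib, on the steroid reading.

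**Effect on a crude proportion (illustration).** Assume the same constant hazard in both arms, no competing risk, and true 24-month incidence I. Then λ = −ln(1 − I)/24 and the proportion seen by month t is 1 − exp(−λt).
- I = 20%: 12.6% by Month 14.5, against 15.4% by Month 18 and 16.9% by Month 19.9
- I = 50%: 34.2%, against 40.5% and 43.7%

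The spurious ruxolitinib excess is about 3 to 10 percentage points. These incidences are assumptions; the protocol gives none.

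**AE reporting to EOT + 180 days.** Control: 70 + 180 = 250 to 77 + 180 = 257 days. Ruxolitinib: 183 + 180 = 363 to 241 + 180 = 421 days. The ratio is 363/257 = 1.4 to 421/250 = 1.7. With CsA counted in controls it is 363/363 = 1.0 to 421/363 = 1.2.

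**The case against.** Several stronger readings are tempting and should be set aside.

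- *AEs are not observed to Month 24.* The protocol sets no Month-24 horizon for AEs; Section 2 says only that they are tabulated and listed. What stands is the unequal window.
- *The AE window is 2.0–2.7 times longer with ruxolitinib.* A reader could get this from "Monitoring for the occurrence of new AEs should be continued for at least 30 days after the last dose of study drug" in Section 7.4.1.2. But 30 days is a minimum, and Section 6.5.1 takes the longest limb, so the 180-day visit governs. The supportable ratio is 1.4–1.7.
- *Recurrent acute GVHD is also unobservable.* The Month-12 horizon in Section 2 lies inside the cap in both arms for patients without an earlier stop, and Section 7.5.1 grades acute GVHD to Day 365 from randomisation. Section 8.3.2 analyses recurrence in a competing-risk framework, which accommodates unequal administrative censoring. What stands is the Month 12/Month 24 conflict, and the clash between uncapped grading in Section 7.5.1 and the cap in Section 6.5.2.
- *The 3.5–5.5-month gap is a fact.* It depends on how control EOT is read, and Day 70–77 is the early case because the control taper starts after CR.
- *cGVHD is definitely not scheduled at Month 24.* Appendix A has a cGVHD row and columns to +36 months, but its marks are missing from the extracted text. They may schedule it.
- *The lack of a fixed TEAE analysis window is an error.* Table windows and exposure-adjusted rates may be in a SAP that is not shown.

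None of this rescues Month-24 cGVHD under Sections 6.5.2 and 7.5.2. Every reading in the table stops short of Month 24, including the one that counts CsA. Competing-risk methods cannot supply an estimate beyond the last planned observation. Nor do they cure stopping at progression or new therapy, which is related to outcome and, if the protocol's assumed Day-28 response rates of 55% and 75% hold, plausibly unequal between arms.

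**Conclusion.** The point holds in this form: Sections 6.5.2 and 7.5.2, followed as written, cannot deliver cGVHD incidence at Month 24 for patients on the planned tapers. The shortfall is about 4 to 10 months. That conclusion does not depend on how control EOT is defined. The difference between arms does: about 3.5–5.5 months if EOT is the end of steroid in controls, and 0–1.9 months if CsA counts. On the steroid reading, crude cGVHD proportions would be biased in favour of controls, and AE reporting would be 1.4–1.7 times longer with ruxolitinib. The recurrence horizon (Month 12 or 24), the safety follow-up length (180 or 365 days) and the duration of acute GVHD grading are further text conflicts. They need reconciling but do not by themselves show bias between arms. The primary Day-28 endpoint is not affected.

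**What to change.** - Sections 6.5.2 and 7.5.2: assess cGVHD to Month 24 from randomisation in both arms at the visits listed in Appendix A, irrespective of EOT, GVHD progression or new therapy. Do the same for recurrent acute GVHD if Month 24 is kept. Bring Section 7.5.1 and the Appendix A marks into line.
- Section 2 and synopsis: state one horizon for recurrent acute GVHD.
- Synopsis and Sections 4.6 and 6.5.1: state one safety follow-up length.
- Section 6.2 or 6.3: define EOT for the control arm, saying whether CsA counts, so that AE collection covers a comparable period from randomisation in both arms.

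The cost is small. Some patients are assessed for longer, at visits the schedule already lists, and the rest is wording. With a common end at Month 24, the planned GVHD windows become 24 and 24 months.
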